**Appendices**

*Appendix S1*

**Summary**

To our knowledge, there is scarce data evaluating the extent of global surgery opportunities at medical schools across the world. Given the International Student Surgical Network (InciSioN) has national working groups (NWGS) across the world, we are in a unique position to establish the global surgery educational practices globally. Establishing an international framework on global surgery exposure and knowledge is important, as it will enable InciSioN to provide support and supplement formal educational practices where needed. This online, international, multi-centre, questionnaire-based study evaluates global surgery exposure, global surgery knowledge and career aspirations among medical students across the world.

**Methods**

Primary aim:

To collect high quality and relevant data regarding global surgery exposure for medical students across the world in order to establish an international framework

Secondary Aims:

To examine students’ awareness of the key messages of the Lancet Global Surgery Commission

To characterise the proportion of medical students who would want to be involved in global surgery in their future career

To ascertain perceived barriers to becoming involved in global surgery

Study Design

The International Survey Of Medical students Exposure to Relevant global Surgery (ISOMERS) study is an online, international, multi-centre, questionnaire-based study evaluating global surgery exposure and career aspirations among final year medical students across the world. Data will be collected on the demographics of participants, their exposure to global surgery, their awareness of the key messages of the Lancet Global Surgery Commission, and their career aspirations. The questionnaire will be disseminated by email and social media through collaborative university medical school and student networks, such as the network of InciSioN National Working Groups (NWGs) across the world. The generic collaborative method, and the benefits that participating students derive from it are based on previous well-documented literature.

Study Population

All medical schools across the world will be eligible to participate. Participant eligibility will be determined according to pre-specified criteria. Responses will be excluded if the participant did not meet the inclusion criteria or met the exclusion criteria. Participation rates will be calculated as the total number of eligible participants over the total number of final year medical students at participating medical schools. The minimum sample size required from our target population for a margin of error of 5% and a confidence level of 95% is 377 assuming a 50% response distribution for each question.

Inclusion criteria:

All final year medical students across the world

Exclusion criteria:

Listed as a collaborative author or named author on any publications from this study.

Primary Outcomes

The proportion of students that have had exposure to global surgery in each country.

The range of modalities utilised by medical students to gain exposure to global surgery.

The percentage of students that prefer each modality.

Secondary Outcomes

The proportion of students aware of the key messages of the Lancet Global Surgery Commission

The proportion of students who do not want to pursue a career in global surgery.

The range of barriers identified by medical students to pursuing a career in global surgery.

Methods for recruiting participants

All final year medical students at any medical school in the world will be eligible to participate. Medical students will be invited to participate in the study by email and social media.

In addition, final year medical students enrolled in any medical school in the world may be invited to collaborate in the study as regional leads as described in Table 1. Collaborators will ensure that the steering committee possess accurate data about the number of final year medical students at their institution, and they will be primarily responsible for disseminating this questionnaire amongst students at their medical school.

Financial and other rewards to participants

No financial or other rewards will be offered to participants.

Data collection

ISOMERS will be delivered by NWGs of InciSioN. Each NWG will be responsible for conducting ISOMERS within their country and disseminating the questionnaire. Medical students enrolled in any medical school may be invited to collaborate in this study as regional leads who are coordinated by the appropriate NWG. The role of a regional lead would be to identify the number of final year medical students at their institution and to disseminate the questionnaire among students at their medical school. Dissemination will be done using any online tools such as social media and mailing lists. The questionnaire must be disseminated by regional leads using all online tools available to them at least once a week for 6 consecutive weeks. Regional leads must share evidence to show that they have done to this to their appropriate NWG to be awarded collaborator status within our collaborative authorship model.

The online questionnaire utilises a combination of the Likert scale, multiple choice options and free text questions in order to broaden the capture and improve granularity of the data. The questionnaire is divided into four major sections: background information, provision of global surgery teaching, knowledge about global surgery and career aspirations. All sections of the questionnaire must be completed for the answers to be deemed eligible. Following data collection, the data will be validated and analysed by the steering committee. The questionnaire has been sent to multiple medical students who were not involved in creating the data collection proforma. Their responses were evaluated for potential problems, and the questionnaire was updated to ensure the questions were relevant, comprehensive and accessible.

Medical schools will be able to request for their own specific data and the analysis done on said data from the ISOMERS steering committee following study completion. InciSioN NWGs will be able to request for their country specific de-identified and pseudo-anonymised data.

Information Governance

No identifiable information will be collected. No individual medical school data will be published with the exception of case studies with permission from the medical school. Data will be collected using a structured standard questionnaire. All data will be pseudo-anonymised. Providing personally identifying data (i.e. contact details) will be optional and will not be linked to the questionnaire answers given. All other data collected may be used for research purposes. Data will be stored securely and accessible only by the primary researchers and users nominated by them. At the end of the project, the data will be stored for five years after final publication.

Statistical Analysis

The resultant data will be analysed via descriptive statistics. For quantitative data where possible, ANOVA tests will be used for parametric data and the Wilcoxon signed-rank test will be used for non-parametric data. For Likert scale data, a multinomial regression will be utilised.

Authorship

In accordance with National Research Collaborative (NRC) authorship guidelines[39] all publication outputs from ISOMERS will be listed under a unified corporate authorship: ‘International Student Surgical Network**’**. Certain publications will include named authors on the bye-line as well as the group name. Anyone who has demonstrated satisfactory completion of the minimum requirements for authorship will be eligible for PubMed-citable collaborative authorship in accordance with the roles defined below:

**Steering Committee:** Responsible for the protocol design, project coordination, and data handling.

**Writing Group:** Responsible for the overall scientific content, data analysis, and preparation of research manuscripts.

**Collaborators:** A network of medical students across all medical schools. They are responsible for leading the study regionally.

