**Conclusion**

The International Survey Of Medical students Exposure to Relevant global Surgery (ISOMERS) will establish whether medical students are exposed to global surgery during medical school, how they are exposed to global surgery, whether the types of exposures meet the needs of students, current global surgery knowledge among students, and career aspirations among students and doctors. This is the first such an endeavour has been undertaken internationally. Our results will allow us to draw comparisons between countries.

*Appendix S2*

PDF attachment

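### Delivery by a global-surgery student network, with no record described of the recruitment channel, is likely to overstate each country's exposure proportion, by an unknown amount that may differ between countries

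*Protocol*

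**What the plan says.** The first primary outcome (Protocol, Methods, Primary Outcomes) is "The proportion of students that have had exposure to global surgery in each country". The Conclusion adds: "Our results will allow us to draw comparisons between countries".

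On recruitment, Study Design says: "The questionnaire will be disseminated by email and social media through collaborative university medical school and student networks, such as the network of InciSioN National" (the network's national groups, called NWGs below). Data collection is more definite: "ISOMERS will be delivered by NWGs of InciSioN. Each NWG will be responsible for conducting ISOMERS within their country and disseminating the questionnaire". Regional leads, coordinated by the NWG, pass the questionnaire on at their own medical school. On the means, the text says: "Dissemination will be done using any online tools such as social media and mailing lists".

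The Summary describes the network's own interest in this education. Of the planned framework on exposure and knowledge it says that "it will enable InciSioN to provide support and supplement formal educational practices where needed".

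Three further provisions bear on the point:
- Leads are to reach students across their medical school, weekly for six weeks, and must show evidence of having done so.
- Anyone listed as a collaborative or named author is excluded.
- A participation rate is calculated against all final-year students at participating schools.

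The Statistical Analysis section names descriptive statistics, ANOVA, the Wilcoxon signed-rank test and multinomial regression.

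**The concern.** The outcome is a population prevalence, but the sample is an open, self-selected one, recruited by an organisation whose subject is the exposure being measured. Contact with that organisation may itself count as exposure. Students who follow its channels are also more likely to know the Lancet Commission's messages and to want a career in the field, so the secondary outcomes face the same risk.

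Two things are at stake. The first is the level: a country's exposure proportion may be too high. The second is the comparison: if the network is more active in one country than in another, part of the difference between them may reflect recruitment and not teaching.

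This is not a matter that can be left to an analysis plan. If the channel is not recorded when the response is collected, no later analysis can recover it.

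**Working it through.** **The plan's own figure.** The stated minimum is 377 for a 5% margin, 95% confidence and a 50% proportion. The formula is n0 = z²p(1−p)/e² = 1.96² × 0.25 / 0.05² = 384.1, or 385 rounded up. With a finite-population correction, n = n0/(1 + (n0−1)/N), an assumed N of 20,000 gives 376.9, or 377. The protocol does not state N. The figure reproduces, but it covers random error only.

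**Bias from membership.** The protocol gives no membership share, response ratio or exposure by membership, so all inputs here are assumptions. Let m be the share of final-year students who are network members, a and b the proportions exposed among members and non-members, and k the ratio of members' response rate to non-members'.

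- True proportion: m·a + (1−m)·b
- Observed proportion: [m·k·a + (1−m)·b] / [m·k + (1−m)]

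Worked case, m = 0.05, a = 0.9, b = 0.3, k = 5: observed = (0.225 + 0.285)/(0.25 + 0.95) = 0.510/1.20 = 42.5%; true = 0.045 + 0.285 = 33.0%.

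| m | a | b | k | True | Observed | Bias (points) |
|---|---|---|---|---|---|---|
| 5% | 50% | 30% | 1.5 | 31.0% | 31.5% | +0.5 |
| 5% | 60% | 30% | 2 | 31.5% | 32.9% | +1.4 |
| 2% | 90% | 30% | 3 | 31.2% | 33.5% | +2.3 |
| 5% | 90% | 30% | 5 | 33.0% | 42.5% | +9.5 |
| 10% | 90% | 30% | 8 | 36.0% | 58.2% | +22.2 |

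**Two countries.** Take a = 90%, b = 30%, k = 5 in both, with m = 2% in one and 10% in the other. Observed: 0.384/1.08 = 35.6% and 0.72/1.40 = 51.4%, a difference of 15.8 points. True: 31.2% and 36.0%, a difference of 4.8 points. About 11 points of the apparent difference come from recruitment.

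**The same question without a membership model.** Let R be the response rate of exposed students divided by that of unexposed students. Then observed p* = pR/(pR + 1 − p). The bias reaches 5 points at R = 1.33 if the true p is 20%, and at R = 1.22 if it is 50%. The worked case above corresponds to an R of about 1.5: observed odds 0.425/0.575 = 0.739, true odds 0.330/0.670 = 0.493, ratio 1.5.

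At n = 377 and R = 1.5, a nominal 95% interval covers the truth about 11% of the time (p = 20%) or 2% (p = 50%). The bias term does not contain n, so a larger sample narrows the interval around the wrong value. If R = 1 there is no bias. If R = 0.8 the bias is downward (20% becomes 16.7%).

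**Testing possible remedies under the same model.**
- A whole-class link: if members still respond five times as often, the result is still 42.5%. The link removes enrichment by channel, not self-selection.
- Comparing non-members only: both countries in the example show 30%, so the genuine 4.8-point difference disappears. This changes what is estimated.
- Weighting to the country's own membership share: 0.05 × 0.9 + 0.95 × 0.3 = 33.0%, which is the true value. This holds if response depends on membership alone and the share is known.

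**The case against.** The strongest objection is that the bias is inferred. A reader might conclude that every country's proportion is biased upwards. The documents do not show that: they give none of the quantities that fix the sign or size, and under mild assumptions the bias is under 1 point. The 5% margin is also stated for a single sample of 377, not for each country, so it serves here only as a rough scale.

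A reader might also take recruitment to be confined to the network. The text does not support this. Study Design names the NWGs as an example, alongside medical school networks, and leads are to reach students throughout their school. Nor does it follow that a country without an NWG has no route into the survey. Students at any medical school may become leads, and students are also invited by email and social media. Coordination by an appropriate NWG is unclear for such countries, but that is an ambiguity and not an absent route.

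Excluding listed authors removes some of the most engaged students and works against overestimation. The participation rate shows where non-response leaves room for bias. Finally, the questionnaire is not shown and may already ask about membership, and stratification or weighting could be set out in an analysis plan that is not at hand.

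These points limit the certainty but do not remove the concern. The author exclusion does not reach ordinary members and followers. The participation rate shows how many students are missing, not which ones. School-wide dissemination by any available tool still leaves the source of each response unrecorded, as far as the protocol describes.

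**Conclusion.** The concern holds as a likely overestimate of exposure, awareness and career interest, of unknown size and possibly unequal between countries. It rests on the documented facts that the NWGs deliver the survey by any online tools, that the outcome is a country proportion meant for comparison, and that no record of channel is described. It also rests on the reasonable, but undocumented, expectation that students reached through the network are more exposed and readier to respond.

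The range of about +0.5 to +22 points reflects the assumed inputs and is not a prediction. The mitigating provisions soften the bias without correcting it, and reaching or exceeding 377 responses does nothing about it.

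**What to change.** 1. Give each regional lead two survey links, one for whole-class lists and one for network or social-media channels. Report each country's exposure proportion by channel. Use the whole-class result as the main estimate or as a pre-specified sensitivity estimate, and state that it removes channel enrichment only and not self-selection.
2. If the questionnaire does not already ask it, add one item on membership of InciSioN or another global-surgery group. Report exposure by membership. Where the national group can supply its count of final-year members, weight to that country's own membership share, which keeps the outcome as defined. Present a comparison among non-members as supportive only.
3. Word the country estimates and the comparisons as applying to responding students at participating schools.

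The cost is one extra link, at most one extra item and a stratified table. Fewer responses will count towards the main estimate if the whole-class result is chosen, and reported exposure will probably be lower. Class sizes are already to be collected by the leads; the member counts would be a new request to the national groups.

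### The minimum of 377 rests on an unstated population of about 20,000, and its 5% margin is a nominal pooled figure that does not carry over to country-level proportions

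*Protocol*

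**What the plan says.** The only sample-size statement is in the protocol, Methods, Study Population: "The minimum sample size required from our target population for a margin of error of 5% and a confidence level of 95% is 377". The same sentence sets the expected proportion at one half, whichever question is considered. No population size is given and no finite-population correction is mentioned.

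Three other places in Methods bear on it:

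- **Inclusion criteria:** "All final year medical students across the world".
- **Study Design, on recruitment:** "The questionnaire will be disseminated by email and social media through collaborative university medical school and student networks".
- **Primary Outcomes, first item:** "The proportion of students that have had exposure to global surgery in each country".

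The Conclusion adds that the results are meant to support comparisons between countries.

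**The concern.** There are two separate matters.

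**The figure cannot be traced.** A reader who puts the three stated inputs into the usual precision formula does not get 377. A population size is needed as well, and the one that works is hard to reconcile with a worldwide target population.

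**The margin is stated without conditions.** The formula gives 5% for one proportion, estimated from all respondents together, in a simple random sample. The planned sample is an open, volunteer sample reached through schools and student networks, and the first primary outcome is estimated country by country. The protocol nowhere qualifies the 5%.

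This is the protocol's only planning number and only precision claim. If the sentence goes unchanged into a publication, reaching 377 responses could be presented as having secured 5% precision for final-year students worldwide, or for each country's result.

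**Working it through.** **Inputs stated in the protocol (Methods, Study Population):** margin d = 0.05; confidence 95%, so z = 1.96 two-sided; p = 0.50. The population size N is not stated.

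**Step 1. The stated inputs alone.**
n0 = z² p(1−p)/d² = 1.96² × 0.25 / 0.05² = 384.15 (with unrounded z), rounded up to 385.

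**Step 2. Reproducing 377.** With a finite-population correction, n = n0 / (1 + (n0 − 1)/N). At N = 20,000:
n = 384.15 / (1 + 383.15/20,000) = 384.15 / 1.01916 = 376.9, rounded up to 377.

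So 377 can be reproduced, but only with N of about this size. Rounding up, N must lie between 17,686 and 20,213. Rounding to the nearest whole number, it must lie between 18,867 and 21,763.

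**Step 3. Larger populations.** The protocol gives no worldwide count, so these values of N are assumptions.

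| Assumed N | Required n (rounded up) |
| --- | --- |
| 20,000 | 377 |
| 50,000 | 382 |
| 100,000 | 383 |
| 500,000 | 384 |
| No correction | 385 |

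**Step 4. What the difference costs.** Margin = z √(p(1−p)/n).
- n = 377, no correction: 1.96 × √(0.25/377) = 5.05%.
- n = 385, no correction: 4.99%.
- n = 377, N = 20,000: 5.00%.

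The shortfall is 385 − 377 = 8 responses, or 8/377 = 2.1%.

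**Step 5. Clustering (illustration only).** Design effect = 1 + (m − 1)ρ, with m respondents per school and within-school correlation ρ. The protocol gives neither. Assume m = 10 and ρ = 0.05 to 0.10:
- ρ = 0.05: design effect 1 + 9 × 0.05 = 1.45; effective n = 377/1.45 = 260; margin 5.05% × √1.45 = 6.1%.
- ρ = 0.10: design effect 1 + 9 × 0.10 = 1.90; effective n = 377/1.90 = 198; margin 5.05% × √1.90 = 7.0%.

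Self-selection adds bias that neither a design effect nor a larger n removes.

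**Step 6. Country level (illustration only).** The protocol fixes no number of countries and no number of responses per country. If 377 responses were split equally:

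| Assumed countries | Responses per country | Margin per country |
| --- | --- | --- |
| 10 | 37.7 | about 16% |
| 20 | 18.9 | about 23% |
| 50 | 7.5 | about 36% |

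The normal approximation is rough at the smallest of these sizes, but the order of magnitude is clear.

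**The case against.** The strongest reply is that nothing practical turns on 377 against 385. At 377 the margin is at worst 5.05%, which is 5% at the precision the protocol uses. The figure is called a minimum; it is neither a cap nor a stopping rule, and no powered test rests on it. Recruitment is governed by weekly dissemination over six weeks (Data collection), with a possible extension (Project Timeline), and the main analysis is descriptive. All of this stands.

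It can also be said that the protocol gives no worldwide count, so a population above 20,000 is not shown by the document. The sentence before the sample size uses the final-year enrolment of the participating schools as the denominator for participation rates, and that might be the N intended. This stands in part: the worldwide size is my assumption. But the protocol does not say that this denominator was used, regional leads have yet to collect those enrolment numbers, and the inclusion criterion is worldwide.

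Finally, the protocol never claims a random sample, the cluster size and correlation in Step 5 come from outside it, and handling of clustering may sit in an SAP that is not shown. The design-effect margins are therefore illustrations, not findings. The point that remains is that the protocol itself states a margin whose formula presumes random sampling, applies it to every question, and attaches no condition.

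A reader might infer that the survey is undersized, or that 377 fails to give a 5% margin. The documents do not support that on the arithmetic: the loss is 0.05 percentage points.

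**Conclusion.** The point holds as a fault in the precision statement, not as a material error in sample size. The stated inputs give 385. The figure 377 depends on an undisclosed population of about 20,000, which does not fit the stated worldwide target if, as assumed, that population is much larger. On its own this is worth at most 8 responses.

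The greater weakness is scope. The 5% is nominal, pooled and conditional on simple random sampling. Recruitment through schools and networks is clustered and self-selected, so the true uncertainty is larger by an amount that the protocol does not allow one to calculate. The margin also says nothing about the precision of the first primary outcome, which is set at country level. That last conclusion needs no assumption; only the 16% to 36% margins depend on an assumed number of countries and an equal split.

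It should be corrected, but it does not invalidate the survey.

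**What to change.** Replace the sample-size sentence with wording to this effect:

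> 385 responses (or 377, if a population of about 20,000 is stated and justified) give a nominal 5% margin of error, at 95% confidence and a 50% proportion, for a proportion pooled over all respondents under simple random sampling. This margin does not apply to country-level proportions, and clustering and self-selection make the true uncertainty larger.

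If a margin under clustering is added, such as about 6% to 7% for a design effect of 1.45 to 1.9, label it an illustrative assumption and state the cluster size and correlation behind it. Report each country's proportion with its own confidence interval and number of respondents.

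The change is one of wording and reporting. No further recruitment is required; the only cost is a slightly less favourable precision statement.

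### The only exclusion criterion turns on an authorship status that regional leads acquire after answering, and the protocol describes no way to find and remove their answers

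*Protocol*

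**What the plan says.** All references are to the Protocol, Methods.

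- **Study Population.** The sole exclusion criterion is being "Listed as a collaborative author or named author on any publications from this study". It is applied to answers: "Responses will be excluded if the participant did not meet the inclusion criteria or met the exclusion criteria".
- **Methods for recruiting participants.** Eligibility is restated without the exclusion: "All final year medical students at any medical school in the world will be eligible to participate". The next paragraph says that "final year medical students enrolled in any medical school in the world may be invited to collaborate in the study as regional leads", so a lead can also meet the inclusion criterion.
- **Data collection.** Leads must disseminate the questionnaire "at least once a week for 6 consecutive weeks", and "Regional leads must share evidence to show that they have done to this to their appropriate NWG to be awarded collaborator status". This section also allows leads from any medical school without naming a year of study, so some leads may not be in their final year.
- **Information Governance.** No identifying data are gathered. On contact details: "Providing personally identifying data (i.e. contact details) will be optional and will not be linked to the questionnaire answers given". Data are described as pseudo-anonymised, but no key or matching step is given.
- **Authorship.** Some publications will carry named authors in addition to the group name. The protocol does not say when the author list closes.

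**The concern.** An eligibility rule has to be decidable either when the person answers or later from the data held. For regional leads this one is neither.

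A lead who answers in the first week does not yet know whether the six-week requirement will be met, and so whether collaborator status will follow. When that is known, the answers carry nothing that ties them to the lead. The rule in Study Population and the data handling in Information Governance do not fit together as written.

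Regional leads work for a student global surgery network. They are plausibly more exposed to the field, more aware of the Commission's messages and more inclined towards such a career than their classmates. If their answers remain, the first primary outcome (exposure by country) would probably be too high. Awareness could move the same way. The career outcome counts students who do not want to pursue global surgery, so it could move downward.

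**Working it through.** **1. Sequence of events**

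| Step | When | Source |
|---|---|---|
| Lead takes up the role | Regional lead recruitment is a separate activity in the timeline | Project Timeline |
| Lead may answer the questionnaire | Any time during data collection | Methods for recruiting participants |
| Collaborator status can be earned | After six weeks of dissemination and submission of evidence | Data collection |
| Authors' answers are to be excluded | Only once authorship is known | Study Population |
| Link from author to answer | None described | Information Governance |

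The role is known early, but the status that the criterion uses is known late. By then no described step connects the author to the answer.

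**2. The plan's own precision figure, as a yardstick**

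Inputs from Study Population: margin 5%, confidence 95%, assumed proportion 50%, stated minimum 377.

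n0 = 1.96² × 0.5 × 0.5 / 0.05² = 384.1.

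With a finite-population correction, n = n0 / (1 + (n0 − 1)/N). At N = 20,000 (assumed; the protocol gives no population size), n = 384.1 / (1 + 383.1/20,000) = 376.9, which rounds up to 377. The figure is reproducible and is not in dispute. It matters here only because it sets 5 points as the planned margin.

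**3. Bias if leads' answers remain**

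Let f be the leads' share of analysed answers, pc the exposure among them, and p the exposure among other students. The protocol gives none of these, so all are assumptions.

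Bias = [f × pc + (1 − f) × p] − p = f × (pc − p).

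| f | p = 30%, pc = 100% | p = 50%, pc = 100% | p = 30%, pc = 80% | p = 50%, pc = 80% |
|---|---|---|---|---|
| 1% | +0.7 | +0.5 | +0.5 | +0.3 |
| 2% | +1.4 | +1.0 | +1.0 | +0.6 |
| 5% | +3.5 | +2.5 | +2.5 | +1.5 |
| 10% | +7.0 | +5.0 | +5.0 | +3.0 |

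(percentage points)

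With pc = 100%, the bias equals the 5-point margin at f = 5/70 = 7.1% for p = 30%, and at f = 5/50 = 10% for p = 50%.

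**4. A small country**

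Take 20 other students plus 2 leads, all leads exposed (assumed numbers).

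- p = 30%: (20 × 0.30 + 2)/22 = 8/22 = 36.4%, a bias of +6.4 points.
- p = 50%: (20 × 0.50 + 2)/22 = 12/22 = 54.5%, a bias of +4.5 points.

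The 95% sampling margin with 20 respondents is itself about 20 to 22 points, so in any one such country the bias is smaller than the random error. Unlike random error, it would probably run in the same direction from country to country.

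**5. Participation rate**

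The numerator counts eligible participants and the denominator counts all final-year students at participating schools. Final-year leads who become authors are meant to leave the numerator but stay in the denominator. A few leads set against a whole final-year class make this a minor inconsistency.

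**The case against.** The strongest reply is that exclusion needs no linkage. Steering committee and writing group members know their roles, and regional leads are coordinated by their NWG. Any of them could be told not to answer, or could declare their role in the questionnaire. The questionnaire is not shown and has a background section in which such an item could sit. The protocol also states the intention to exclude. A reader might infer that the criterion can never be applied and that collaborators' answers therefore stay in and inflate exposure. The documents do not support that: they show only that no means of applying the rule is described. This part of the objection stands. It does not fully rescue the wording, because a question about present role would apply a different criterion from the one written, and a lead part-way through the six weeks cannot reliably answer the written one.

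The size is also open to challenge. No document says that collaborators are nearly all exposed, how many are in their final year, or how many would answer. Leads who are not in their final year fail the inclusion criterion anyway. That stands, and the effect overall could be negligible.

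A further argument is that final-year leads belong to the target population, so only their over-representation is bias. That would hold if the target were all final-year students. The protocol chose to exclude authors, so the answers it intends to analyse are those of non-authors, and the formula above follows that choice.

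Finally, a lead who misses the evidence requirement stays eligible while an equally involved lead who meets it does not. That is a question of where to draw the line. It is not an error in itself.

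**Conclusion.** The point holds in a limited form. For regional leads the exclusion rests on a status settled after the six weeks of dissemination, and the data described give no way to find their answers afterwards. Answers from final-year leads may therefore remain. Eligibility belongs in the protocol, so this is not a detail that can be left to an analysis plan.

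The direction for exposure is probably upward, as an inference from how leads are recruited. The size is unknown. With all leads exposed and 30% to 50% of other students exposed, it is 0.5 to 0.7 points at a 1% share of answers and 5 to 7 points at 10%. It reaches the planned margin only at a share of about 7% to 10%. One or two leads could produce that share in a country with few respondents, but it would take many more in the pooled sample. The documents do not establish that exposure will be inflated. They establish that the protocol has no stated safeguard against it.

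**What to change.** Define the exclusion by the role held when answering: anyone who is, or has agreed to act as, a regional lead, NWG organiser, or steering committee or writing group member for this study. Make this a compulsory first screening question and exclude those who answer yes, whether or not authorship is later awarded. This needs no names and leaves the data-handling rules unchanged. If the questionnaire already contains such an item, only the protocol wording needs to change.

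Repeat the exclusion in the eligibility sentence under Methods for recruiting participants. For consistency, subtract final-year students in these roles, whose number the NWGs can supply, from each school's denominator for the participation rate. The effect of that step is minor.

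The cost is one question and one sentence of protocol text. The downside is that a few answers from leads who never become authors are dropped. The rule also still relies on honest self-declaration.
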